## 12. Methods and Procedures - Prospective Studies

- 12.1. Describe in detail the design and methodology of the study. Provide a detailed description of the planned data collection, specific outcomes, and criteria for evaluation and endpoint definition. If applicable, include information on stratification or randomization plans. Include the frequency and duration of each activity and the total length of subject participation. Identify and distinguish between those procedures that are standard of care and those that are experimental. (Refer to specific sections of the protocol/grant, if applicable. Describe any differences between the protocol and the local site.)**

A stratified and randomized control trial will be conducted to examine the specific aims of the proposed study. Each eligible patient will be randomized to one of two groups, standard of care or standard of care plus virtual reality (VR). A balanced randomization scheme will be used to balance the age and gender distribution of the two study groups.

### Stratified Randomization Design

Contingent on randomization, the patient will undergo the medical procedure either according to CHLA's standard of care (control) or the patient will participate in the VR plus standard of care (VR) condition. In order to balance the number of patients by gender, we will use a stratified randomization scheme for assignment of patients into study groups. Gender will be divided into two strata. Within each gender stratum, a balanced randomization scheme will be generated to assure equal number of VR and standard of care subjects. At the beginning of the project, the investigative team will develop the randomization schema within SPSS 22.0 that will be used for the proposed recruitment design. For implementation, the investigative team will refer to the list generated by the randomization program to determine which condition the next study subject will be assigned to. This list will be divided into the two gender groups described above.

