The Mira Prism is a portable, augmented reality (AR) HMD powered by iPhone. When paired with the iPhone, the Mira Prism goggles can superimpose computer-generated images on the user's view of the real world. Unlike the full immersion of VR, AR allows users to view the outside world while interacting with digital content. In this study, the patient can interact with Magic Mallet (developed by Miney Moe). Magic Mallet is a distraction game designed for pain management and communication during procedures. The game automatically adjusts cognitive load for optimal effect for users. Study team iPhones specifically loaded with Magic Mallet, and without cellular capability, will be used with the Mira Prism.

We will ensure that the Mira Prism is not used with patients who have symptoms of "squint, amblyopia, or anisometropia" through our eligibility screening of all patients, performed prior to the informed consent process. One of the exclusion criteria in our study is "Children with visual, auditory, or tactile deficits that would interfere with the ability to complete the experimental tasks or use the technological devices." We will not enroll children with any visual deficits.

The manuals for Oculus Go and Mira Prism both state that these devices should not be used by children under 13 years of age because the headset is not sized for children and improper sizing can lead to discomfort. This warning has to do with hardware design rather than actual safety. Both devices have been used across the country by children under 13 years of age. We will always tighten the adjustable straps of these devices to ensure that they are comfortable for children under 13 years.

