### Patient Procedures and Data Collection

After informed consent and assent have been obtained and the patient has successfully met the screening criteria for cognitive ability, the patient and his/her caregiver will be enrolled into the study. Patients and their caregivers will be asked to fill out several questionnaires via Qualtrics on an individual IPAD (see uploaded Table of Measures) in the private area/room.

In order to ensure that pre-existing pain or anxiety do not contaminate reports of procedural pain or virtual reality-related symptomatology, the patient will be asked to report pre-procedure baseline levels for the following measures: the Visual Analog Scale (VAS), the Faces Pain Scale Revised (FPS-R), the Colored Analogue Scale (CAS) for pain, the VAS for procedural anxiety, the Facial Affective Scale (FAS), the Childhood Anxiety Sensitivity Index (CASI), and the Malaise Scale. If patient is age 18 or above, they will also complete a demographic form. This is expected to take approximately 15 minutes.

After patients have completed the pre-procedural battery on the IPAD, and patients and caregivers will be informed about their assigned study condition (VR or standard of care). Children in the VR distraction groups will then begin interacting with the virtual environment for approximately 5 minutes. Following the 5-minute VR primer period the procedure will commence. Following the procedure, children will continue to play the VR game for approximately 2 minutes. Children in the standard care control group will undergo the medical procedure according to the existing CHLA protocol. Regardless of treatment condition, the Research Assistant will observe and record the behavior of the child while s/he is undergoing the medical procedure. A video tape recording of the procedure will also be obtained (if the child, caregiver, and healthcare provider have agreed to be recorded) in order to later score the behavior of the child according to the Child-Adult Medical Procedure Interaction Scale – Revised (CAMPIS-R). Video will be focused on the patient/caregiver and not on the healthcare provider. However, it is possible that the healthcare provider's voice or appendage will be recorded while interacting with the patient and therefore their verbal consent will be obtained as well. Video recording will later be coded for signs and symptoms of anxiety and behavioral distress in the patient and his/her caregiver.

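### As written, the investigative team holds and reads the pre-made randomization list, and nothing described conceals the next assignment from those who screen or enrol

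*Protocol*

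**What the plan says.** All of this is in Protocol section 12.1.

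- **Making the list.** Under Stratified Randomization Design, at the start of the project "the investigative team will develop the randomization schema within SPSS 22.0 that will be used for the proposed recruitment design".
- **Form of the list.** "Within each gender stratum, a balanced randomization scheme will be generated to assure equal number of VR and standard of care subjects". For use, "This list will be divided into the two gender groups described above". No block size is given.
- **Using the list.** "the investigative team will refer to the list generated by the randomization program to determine which condition the next study subject will be assigned" to.
- **Screening.** Under Virtual Reality Technology, visual problems are to be caught by "our eligibility screening of all patients, performed prior to the informed consent process". Under Patient Procedures and Data Collection, a cognitive screen must also be met before the patient is enrolled.
- **Disclosure.** The same section says: "After patients have completed the pre-procedural battery on the IPAD, and patients and caregivers will be informed about their assigned study condition". This concerns families. It says nothing about when staff learn the arm.

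**The concern.** Allocation concealment means that whoever decides whether and when a child enters the trial cannot know which arm comes next. The protocol instead describes a list that exists in advance, is made by the investigative team and is read by that team. Someone who knows the next entry could approach, defer or screen out a child accordingly, without intending to. A child who looks anxious or afraid of needles is the obvious example. The arms could then differ in prognosis before treatment begins.

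This trial has few other protections. The headset is visible to the child, caregiver, provider and the research assistant observing the procedure. The outcomes are mainly subjective reports, together with observed behavior. The video raters are described as independent of each other, but no blinding to arm is described. The comparison therefore leans heavily on sound allocation.

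**Working it through.** The plan states no figure on this point, so the main check is to follow one child through the steps that the protocol describes.

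1. **Before the child arrives.** The gender-specific list is complete and the next entry for that gender is fixed. The team made the list and is the party that consults it.
2. **Eligibility screening.** The team does this before consent. The next entry already exists.
3. **Consent, assent and cognitive screen.** These precede enrolment. The protocol does not name who performs them.
4. **Baseline battery.** Pain and anxiety scales are completed.
5. **Disclosure.** Patient and caregiver learn the arm.

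The delay at step 5 keeps families' knowledge of the arm out of the baseline self-reports. It does nothing at steps 1 to 3, where staff decide who enters. No step mentions envelopes, central or electronic release, an independent holder of the list, or a split between list-keeping and recruitment.

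**Illustration of size.** The protocol gives no figure for steering, so these inputs are assumptions:

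- fraction of VR slots steered: 10% or 20%;
- prognostic gap between the child who fills the slot and the child who otherwise would have: 1 SD in expected pain;
- control arm unchanged and no baseline adjustment.

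Bias = fraction × gap:

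- 0.10 × 1 = 0.10 SD
- 0.20 × 1 = 0.20 SD

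From section 12.2: 100 evaluable patients per procedure type, so 50 per arm, and a two-sided test at 0.05.

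Standard error of the difference in SD units = √(2/50) = 0.20.

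False-positive rate with no true effect = Φ(b/se − 1.96) + Φ(−b/se − 1.96):

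- b = 0.10: b/se = 0.5; Φ(−1.46) + Φ(−2.46) ≈ 0.079
- b = 0.20: b/se = 1.0; Φ(−0.96) + Φ(−2.96) ≈ 0.170

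At 60 per arm (all 120 recruited patients evaluable) the same shifts give about 0.085 and 0.195. A larger sample does not reduce the bias. It makes a false positive more likely.

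**Scale.** At 50 per arm, 80% power corresponds to a difference of about 0.57 SD, so 0.10 SD is 0.10/0.57 ≈ 18% of it. Against the effect size of about 1.5 that section 12.2 assumes, it is 0.10/1.5 ≈ 7%.

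**The case against.** **The list may not be open to recruiters.** A reader might infer that everyone who recruits can see every upcoming assignment, or that the person reading the list is the person who enrols. The protocol says neither. It speaks of one investigative team, does not say how the list is stored, and describes consent and the cognitive screen without naming who does them. This objection stands against the stronger reading. It does not supply a safeguard: the team that screens is not separated from the team that consults the list.

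**Roles may be set out elsewhere.** The text at hand begins at section 12, and eligibility criteria clearly exist outside it. That limits certainty about who does what. However, the section on randomization does describe how assignments are obtained, and that procedure is the one at fault.

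**Baseline data offer protection.** A reader might infer that nothing later could correct such a bias. That is not so. Baseline pain and anxiety are collected so that pre-existing levels do not contaminate the procedural reports. Section 12.2 plans control for baseline variables where applicable, a baseline comparison between arms, and covariates that may include previous experience with the procedure. An anxious child is partly what these measures capture. The objection stands in part: adjustment would reduce the bias, but only for what is measured, and it does not replace concealment.

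**The size is assumed, and so is its direction.** Both points are right. Steering anxious children towards VR would bias against VR. The figures show sensitivity and are not an estimate.

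**Conclusion.** The point holds as a fault in the written procedure. The protocol makes upcoming assignments accessible to the investigative team before a child is approached or screened, and describes no concealment from those who screen or enrol. Delayed disclosure to families does not close that gap. Because the protocol itself fixes the procedure, this is not a detail left to a statistical analysis plan.

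Selection bias is possible. The documents do not show that it occurred, or that every recruiter can see the list. Its size is unknown. The 0.1 to 0.2 SD bias, and the false-positive rate of about 0.08 to 0.17 in place of 0.05, rest on the assumed steering, the assumed 1 SD gap, 50 per arm and no adjustment. Planned baseline control would lower them by an amount that cannot be stated from the documents. The correction belongs before recruitment, since analysis cannot fully undo selective entry.

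**What to change.** Replace the sentence on consulting the list with a release rule:

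- Each assignment is released only after eligibility, consent, the cognitive screen and the baseline battery are recorded, and the time of release is logged.
- Release is through the electronic survey system already used on the iPad, if it supports this, or otherwise through sequentially numbered sealed opaque envelopes, one series per gender.
- The list is kept from anyone who screens or enrols.
- Block sizes vary at random within each gender stratum and are not disclosed to recruiting staff. The treatment is visible, so staff who remember past assignments could otherwise predict the end of a fixed block.

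Families can still be told the arm after baseline, as now planned. The cost is a short wording change and minor set-up work, with no extra patients. Someone must prepare and hold the list without recruiting. The documents do not describe staffing, so the team should check whether that person is already available. Electronic release would keep this need small.

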### 12.2. Describe the statistical considerations for the study, how the sample size was determined, and how the results will be analyzed, if applicable. *(Refer to specific sections of the protocol/grant, if applicable)*

Power analyses based on preliminary data from the PI's previous VR and phlebotomy study determined that 100 participants are needed for the current study. The power calculation is based on the pain intensity VAS, which is calculated as a continuous (0 to 100) variable. 120 patients will be recruited for each type of painful medical procedure to account for attrition/drop out. In other words, 120 patients receiving venipuncture will be recruited, and a separate 120 patients receiving IV placement will be recruited. A total sample size of 100 patients per medical procedure type would result in 25 patients in each of the 4 age-gender strata groups. In our earlier preliminary data the VR pain score was about half that of the other methods giving an effect size of about 1.5. This would result in 80% power for a 2-sided t-test at the .05 significance level. Because we have several covariates planned in this study, we will increase the required sample size by (at least) 20% to allow for adjustment of the covariates. A general rule of thumb is to increase the sample size by 10-20% for each major covariate. Therefore, the proposed sample size of 240 (120 per procedure), assuming some attrition/drop-out will result in more children in each group.

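### The randomization list is split by gender only, although the protocol claims age balance and counts four age-gender strata; it also does not say whether each procedure has its own list

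*Protocol*

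**What the plan says.** Three places in the protocol describe the stratification.

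- The opening of section 12.1 states the aim: "A balanced randomization scheme will be used to balance the age and gender distribution of the two study groups".
- Stratified Randomization Design gives the rule the team will follow. Its purpose is gender balance: "In order to balance the number of patients by gender, we will use a stratified randomization scheme". It then says "Gender will be divided into two strata", sets 1:1 allocation in each ("Within each gender stratum, a balanced randomization scheme will be generated to assure equal number of VR and standard of care subjects") and describes the list itself: "This list will be divided into the two gender groups described above". Neither age nor procedure type appears.
- Section 12.2 assumes a finer structure: "A total sample size of 100 patients per medical procedure type would result in 25 patients in each of the 4 age-gender strata groups". It also separates recruitment by procedure: "120 patients receiving venipuncture will be recruited, and a separate 120 patients receiving IV placement will be recruited".

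The Statistical Analysis section names child age and gender as possible covariates, to enter the multivariate analyses only if they prove significantly related to the outcomes. Procedure type is not named there as a factor.

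**The concern.** Two strata and four strata cannot both describe the same list. Whoever generates it from Stratified Randomization Design will produce one without the age balance claimed in section 12.1 and without the strata counted in section 12.2. Whoever tries to produce the four strata will find no age cut in the text shown.

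A second point is left open. The sample is sized within each procedure, but the randomization text does not say whether each procedure has its own list. If a single gender-split list runs across both, equal arms within a procedure are not assured.

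At stake is precision and protection against chance imbalance in age, a variable the protocol itself treats as likely to matter. The analysis rule does not fully make up for a missing age stratum, because adjustment for age depends on a significance result. The list is drawn up at the start of the project, so it cannot be corrected for patients already allocated.

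**Working it through.** **Inputs.** From section 12.2: 100 patients per procedure before inflation, 120 recruited per procedure, four age-gender strata. From Stratified Randomization Design: two gender strata, 1:1 within each. Assumed for the imbalance figures: each gender list ends exactly 1:1, and gender, age band and procedure groups are equal in size.

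**1. The plan's own figures.** 100/4 = 25 per stratum, 100 × 1.2 = 120 per procedure and 2 × 120 = 240 in total. All three reproduce, but the 25 needs four strata.

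**2. The list as written.** With two gender strata, 100/2 = 50 per stratum. A list matching section 12.2 would need 2 genders × 2 age bands = 4 strata in each of 2 procedures, or 8 sub-lists. At 100 per procedure each holds 25 (12 or 13 per arm). At 120 per procedure each holds 120/4 = 30 (15 per arm). Stratifying equalizes the arms inside a stratum but not the sizes of the strata, so 25 in each also presumes equal recruitment by age and gender.

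**3. Age imbalance if each procedure has its own gender-split list.** Each gender list has 60 patients, 30 of them VR, with 30 in each age band. The VR count in one age band of one gender is hypergeometric:

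- variance = 30 × 0.25 × (30/59) = 3.81
- both genders: 2 × 3.81 = 7.63, SD = 2.76
- the VR-minus-control difference among the 60 patients of that age band has SD 2 × 2.76 = 5.5

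Simulation (50,000 runs) gives a mean absolute difference of about 4 and a 95th percentile of 10; about 10% of lists differ by 10 or more. A difference of 10 is a 35:25 split. With 60 per arm, the share of that age band then differs between arms by 35/60 − 25/60 = 1/6. An unadjusted comparison would carry one sixth of whatever the mean outcome difference between age bands is. The protocol does not give that difference.

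**4. Imbalance if one gender-split list serves both procedures.** Each gender list has 120 patients, 60 of them VR, with 60 in each procedure:

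- variance of the VR count per gender = 60 × 0.25 × (60/119) = 7.56
- both genders: 15.13, SD = 3.89
- 95% range around 60: 60 ± 1.96 × 3.89 = 52.4 to 67.6; simulation gives 52 to 68
- simulated probability of being off target by 6 or more: about 15%

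An age half of 120 patients behaves in the same way.

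**5. What the unequal arms cost.** Effective size at a split of 52:68 is 4 × 52 × 68/120 = 117.9. The loss is 1 − 117.9/120 = 1.8%, and that is at the edge of the 95% range.

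**The case against.** The strongest reply is that little harm follows. Allocation within gender is still random, chance imbalance is already reflected in the standard error, and even a 52:68 split costs under 2%. The protocol also provides for age in the analysis: it is a named candidate covariate, and the sample was raised by at least 20% for covariate adjustment. All of this stands, and it limits the severity. It does not remove the contradiction about age, and conditional adjustment is weaker than a pre-specified term.

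Four stronger readings are tempting, and the document does not support them.

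- A reader might infer that one list certainly runs across both procedures. The text is silent. Separate gender-split lists fit the separate recruitment targets equally well, so this is an omission to settle and not a contradiction.
- A reader might infer that the procedures will be pooled without a procedure term. The analysis text refers neutrally to a painful procedure, and such detail is commonly left to a statistical analysis plan.
- A reader might put the cost at 10–20% of the sample. That needs age and procedure to explain 10–20% of the variance in VAS pain, for which the protocol gives no source. It also measures the cost of omitting covariates from the model, not of how the list is split, and it overlooks the provision to adjust for age.
- A reader might see confounding because headsets depend on age. Three of the four devices cover the whole range of 10–21 years, and headset choice exists only in the VR arm. It could modify the effect but does not confound the comparison of arms.

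**Conclusion.** The point holds for age as an explicit inconsistency: the protocol states a property, age balance through four strata, that its operative randomization rule does not have. That finding needs no assumption beyond the text. For procedure, the point is only that the rule does not say whether lists are separate.

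The size is modest. Stratum size is 50 under the rule as written, against the stated 25. The range of 52 to 68 and the loss of under 2% apply only if a single list serves both procedures. Age imbalance can occur under either arrangement. Every imbalance figure assumes equal-sized groups and lists that finish exactly 1:1. Randomization remains valid, so this is a matter of chance imbalance and precision, and it should be fixed without being treated as a flaw that invalidates the trial.

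**What to change.** Make the opening of section 12.1, Stratified Randomization Design and section 12.2 agree, in one of two ways:

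1. Generate the list within gender × age band, stating the age cut, separately for venipuncture and IV placement, with varied block sizes; or
2. Keep gender as the only stratification factor, delete the claim of age balance and the count of four strata, and state whether each procedure has its own list.

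In either case, pre-specify gender and age as fixed terms in the arm comparisons, in place of entering them only when significant. Add procedure as a fixed term in any pooled analysis.

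The first option costs a regenerated list, edits to three places and a few incomplete blocks at the end of recruitment. It also makes the next assignment somewhat easier to guess: the team consults the list directly, the assigned condition is disclosed to patients and caregivers, and small blocks in eight cells are more predictable than long lists. Varied block sizes reduce that risk but do not remove it. The second option costs only text edits, and it relies on the pre-specified age term to deal with chance imbalance.
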